#### 2.2.3. Randomization

Tasks and conditions will be randomized to avoid familiarization or learning effects. Randomization will be conducted using a random number generator (Random Number Generator tool; Google, LLC., Mountain View, CA, USA). Firstly, the order of application of the tDCS intensities on the three study days (1 mA, 2 mA, and sham) will be randomized. Secondly, the order of the execution of the tasks in the different tests will be randomized: balance (eyes open (EO), eyes closed (EC), EO-DT, EC-DT); strength (isokinetic dynamometry (ID), ID-DT). Thirdly, subtractions from an even or odd number will also be randomized.

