## 2. Materials and Methods

### 2.1. Study Design

This study is a double-blind, sham-controlled, crossover study. All participants will randomly participate through all conditions (1 mA, 2 mA, and sham). This study, in order to fulfil correctly the items of the standard protocol for clinical trials, has followed the SPIRIT 2013 Statement Items [55].

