#### 2.2.2. Recruitment

Taking into account the results of a previous investigation [56], a sample size of 13 achieves 99% power to detect a mean of paired differences of 3.5 with an estimated standard deviation of differences of 2.5 and with a significance level (alpha) of 0.05 using a two-sided Wilcoxon test assuming that the actual distribution is normal. 

Therefore, the sample will be collected during January/February 2022. One group will be composed of women with FM (*n* = 13) from the local association of persons with fibromyalgia, named AFIBROEX, while the other group will be composed of healthy women (*n* = 13).

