### 2.6. Data Analysis

The outcome results will be included in an anonymous dataset to conduct the statistical analyses. Descriptive and quantitative analyses will be reported. The Statistical Package for the Social Sciences (SPSS, version 24.0; IBM Corp., Armonk, NY, USA) will be employed. Due to the sample size, nonparametric statistical analyses can be the most adequate approach.

In this regard, differences between conditions (1 mA, 2 mA and sham), in all the outcomes, will be analyzed using the Kruskal–Wallis test. Post hoc analyses will be conducted using Mann–Whitney-U tests. Subgroups will be used to study if there are differences in treatment effects according to the presented symptomatology. Furthermore, the [r] effect size will be calculated [95]. Therefore, results will include medians, interquartile ranges, the effect size, and the statistical significance. In order to avoid type I error derived from multiple comparisons, the alpha level of significance will be adjusted according to the Benjamini–Hochberg procedure [96]. 

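### No balancing of the six condition orders is stated for 13 women per group, and the named tests have no session term, so a chance imbalance in order would stay uncorrected

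*Protocol article*

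**What the plan says.** Section 2.1 (Study Design) gives the design: "This study is a double-blind, sham-controlled, crossover study". Every woman passes through 1 mA, 2 mA and sham on three study days, at least seven days apart (section 2.4, Intervention).

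Section 2.2.3 (Randomization) states the purpose, "Tasks and conditions will be randomized to avoid familiarization or learning effects", and the tool, "Randomization will be conducted using a random number generator". For the conditions it says that "the order of application of the tDCS intensities on the three study days (1 mA, 2 mA, and sham) will be randomized". It mentions no block, Latin square or other restriction on the orders, and no separate list for the two groups. Nor does it call the draw simple or unrestricted.

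Section 2.2.2 (Recruitment) sets 13 women with fibromyalgia and 13 healthy women.

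Section 2.6 (Data Analysis) says that "differences between conditions (1 mA, 2 mA and sham), in all the outcomes, will be analyzed using the" Kruskal–Wallis test, followed by Mann–Whitney tests. It mentions no session or sequence term, and it does not say whether raw post-stimulation values or changes from the same day's pre-stimulation values are compared.

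**The concern.** The article itself names learning as the threat and gives randomisation of order as the protection. Randomising order makes the learning effect zero on average over many hypothetical trials. It does not make it zero in one trial of 13 women per group. If sham happens to fall early more often than 2 mA, a plain session-to-session gain appears as a 2 mA effect.

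The physical and cognitive tasks are done before and after stimulation. Read as applying to each of the three sessions, that makes six performances per woman, so some practice effect is plausible.

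Two things could limit the damage: balancing the orders at allocation, or removing a session effect in the analysis. The article states neither. At stake are the contrasts among 1 mA, 2 mA and sham, including the hypothesis that intensity makes no difference. Comparisons of tDCS effects between fibromyalgia and control women are also exposed if chance gives the two groups different orders.

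**Working it through.** **The plan's own figure.** Section 2.2.2 states that "a sample size of 13 achieves 99% power". Its inputs are an average paired difference of 3.5, an SD of 2.5 for those differences, alpha 0.05 and a two-sided Wilcoxon test. Simulating the exact signed-rank test with these inputs gives 99.4%. The noncentral-t approximation with n multiplied by 3/π also gives 99.4%. The stated 99% is reproduced and is not in question.

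**Inputs.** From the article: three conditions, hence 3! = 6 orders; 13 women per group; mean paired difference 3.5; SD of differences 2.5. Assumed: each woman's order is drawn independently and with equal chance from the six; a constant shift λ per session; outcomes compared as raw values across sessions.

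**How uneven the orders become (n = 13).**
- P(at least one order unused) = 6(5/6)^13 − 15(4/6)^13 + 20(3/6)^13 − 15(2/6)^13 + 6(1/6)^13 = 0.5608 − 0.0771 + 0.0024 − 0.0000 + 0.0000 = 48.6%.
- P(as even as possible, 2-2-2-2-2-3) = 6 × 13!/(2!^5 × 3!)/6^13 = 1.5%.
- P(first-day counts of the three conditions differ by 4 or more) = 47% (200,000 simulated draws).

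**Gap in mean session position between two conditions.** Within one woman the gap is ±1 in four of the six orders and ±2 in two, so its mean is 0 and its variance is (4×1 + 2×4)/6 = 2.
- Independent draws: SD = √(2/13) = 0.39 sessions. By simulation, the 95th percentile of the absolute gap is 0.77. A given pair is 0.5 sessions or more apart in 20% of draws, and at least one of the three pairs is in 41%.
- Balanced list, each order twice plus one woman: only the 13th woman contributes, so the gap is at most 2/13 = 0.15 and its RMS is √2/13 = 0.11.
- Difference in gap between two independently drawn groups: SD = 0.39 × √2 = 0.55.
- Both groups pooled (n = 26): an order is unused in 5.2% of draws, and the SD of the gap is √(2/26) = 0.28.

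**Effect on a contrast.** The documents give no learning effect, so λ is set to 0, 0.2, 0.5 and 1.0 SD of differences per session (0, 0.5, 1.25 and 2.5 units). The test simulated (40,000 runs per row) is the paired Wilcoxon of the sample-size statement, because it isolates the effect of order. The rates are not those of the Kruskal–Wallis test.

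| λ (units) | RMS chance error, independent draws (0.39λ) | Type I, independent draws | Type I when gap ≥ 0.5 | Type I, balanced list | Power, independent draws | Power, balanced list |
|---|---|---|---|---|---|---|
| 0 | 0 | 4.8% | 4.9% | 4.8% | 99.4% | 99.4% |
| 0.5 | 0.20 | 4.6% | 5.9% | 4.1% | 99.1% | 99.2% |
| 1.25 | 0.49 | 5.0% | 12.7% | 1.8% | 95.8% | 97.3% |
| 2.5 | 0.98 | 5.1% | 20.9% | 0.2% | 70.8% | 77.2% |

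Power falls even with balanced orders because the session shift adds scatter to the paired differences. Their SD becomes √(2.5² + 2λ²), which is 2.60, 3.06 and 4.33 for the three non-zero shifts. Only a session term, or within-session change where the shift is stable within the day, takes that scatter out.

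**The case against.** The strongest reply is that independent draws are an inference. The article names a tool and says nothing about restriction. A random number generator can equally pick from a balanced list, and a condensed article may leave that detail to the full protocol. This stands: a reader might infer that simple randomisation is planned, but the text does not say so, and the figures for independent draws are conditional on that assumption.

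A reader might also infer systematic bias or an inflated error rate. The calculation does not support this. The expected gap is zero and overall type I error lies between 4.6% and 5.1%. It rises only among draws that are already uneven.

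Other protections exist. A pre-stimulation assessment in the same session would let within-session change remove a stable session shift, and the strength test has a familiarization phase. The first is real but unconfirmed, since section 2.6 does not say that change is analysed. Change scores would also carry a session effect if the practice gain from pre to post shrinks over the three days, which is an assumption. For EEG, HRV and sway, a steady gain per session is not shown by anything in the article.

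Finally, balancing alone buys little: 99.2% against 99.1% power at the smallest shift, and 77.2% against 70.8% at the largest. That also stands, and it is why the remedy needs the analysis as well as the list. It does not remove the point, because the tests that the article does name cannot correct an imbalance if one occurs.

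**Conclusion.** The point holds as a low-cost improvement in design and analysis, not as an error that invalidates the trial. As written, a random draw of order is the only stated protection of the condition contrasts against session effects. With 13 women, which is not a multiple of six, that draw is unlikely to be even if it is independent: 49% chance of an unused order, and a gap SD of 0.39 sessions against a ceiling of 0.15 with a balanced list.

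The consequence is chance error and lost precision. Against the planned difference of 3.5, the RMS chance error is 0.20 units (6%) at an assumed shift of 0.2 SD per session, which is small. It is 0.49 (14%) at 0.5 SD and 0.98 (28%) at 1.0 SD, which is material.

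The conclusion rests on three assumptions: independent draws, a constant between-session shift of a size that the documents do not give, and comparison of raw values across sessions. The sample-size statement is unaffected.

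**What to change.** 1. Before the first allocation, prepare a concealed list for each group separately (fibromyalgia, control). Use each of the six orders twice, put the 13th woman on a randomly chosen order, and put the 13 entries in random order. State this in section 2.2.3. If a balanced list already exists, one sentence saying so is enough.
2. In section 2.6, replace the comparison across conditions with a within-woman analysis that adjusts for session, for example a mixed model with condition and session as fixed effects and woman as a random effect. A session term cannot simply be added to the Kruskal–Wallis test.
3. State whether the response is the post-stimulation value or the change from the same session's pre-stimulation value.

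The list costs only its preparation, with no extra women or visits. The second step is a real change to the stated analysis, but it needs no further data. Exact balance would need 12 or 18 women per group. That is not necessary, because the remaining gap with 13 is at most 0.15 sessions.

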### 2.3. Ethical Approval

The study protocol has been approved by the Research Ethics Committee of the University of Extremadura (192/2021).

### 2.4. Intervention

The transcranial direct current stimulation (tDCS) will be conducted with an 8-channel hybrid EEG/tDCS wireless neurostimulator (Starstim, NEuroelectrics, Barcelona, Spain). The electrodes used will be sponge electrodes (Sponstim^®^, 5.65 cm de diameter, 25 cm^2^ surface area) soaked in saline solution. 

Since the DT involves the prefrontal cortex in the main role [23], the active electrode will be placed on the left prefrontal cortex, corresponding to the F3 region of the international 10–20 electrode placement system. The return electrode will be placed on the contralateral supraorbital region (Fp2) [27,44,45,46,48,49,57,58]. At the same time, the HRV and EEG signals will be recorded at Cz, C4, P3, P4, and Oz. Patients will receive tDCS at an intensity of 1 mA (Condition 1) or 2 mA (Condition 2) for 20 min, with a ramp up and ramp down of 30 s each. A duration of 20 min will be applied to ensure that the acute effects remain for at least 1 h [30]. For the placebo or sham condition (Condition 3), the mode included in the NEuroelectrics NIC1 program will be used, consisting of a double sham with a 30 s double ramp up and ramp down. These parameters for Condition 3 were chosen based on previous reports of perceived skin sensations, which generally disappear within the first 30 s [59,60]. 

There will be a minimum of seven days between conditions. One stimulation session will be applied each week. A different stimulation will be applied each week. In total, three weeks are estimated for each participant to complete the study. The intervention and all assessments will be carried out at the Faculty of Sport Sciences (Caceres, Spain).

### 2.5. Procedures and Outcome Measures

#### 2.5.1. Procedure

Figure 1 shows the timeline of the study and the course of the intervention. First, an anthropometric measurement will be carried out to calculate the body mass index (BMI) of the participants. Secondly, participants will answer a series of sociodemographic questions and complete the following questionnaires: (1) International Physical Activity Questionnaire (IPAQ), (2) Fibromyalgia Impact Questionnaire-Revised (FIQ-R), (3) Falls Efficacy Scale International (FES-I), (4) EuroQol 5 dimensions-5 levels (EQ-5D-5L) and (5) Pittsburgh Sleep Quality Questionnaire (PSQI).

Pre-tDCS: After completing the questionnaires, a 5 min baseline EEG recording will be performed. This will be followed by the cognitive test (MoCA), during which EEG will also be recorded. This is followed by the physical (balance and strength) and cognitive tasks in single and dual conditions. In this part of the intervention, the creativity tasks will take place between the two physical tests. During the performance of these tests, brain and cardiac electrical activity will be recorded with EEG, and HRV. 

tDCS: The prescribed intensity will be applied in each session for 20 min (sham, 1 mA, and 2 mA). At the end of each tDCS session, the sensations experienced during the stimulation will be assessed using the sensations related to the Transcranial Direct Current Stimulation questionnaire.

Post tDCS: A 5 min EEG recording will be performed. Furthermore, physical, cognitive, and creativity tasks (in this order) will be performed again while EEG and HRV are recorded. 

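### The test battery runs in a different block order before and after tDCS, and the pre-tDCS values have no stated role in the analysis

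*Protocol article*

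**What the plan says.** Section 2.5.1 (Procedure) has each woman do physical, cognitive and creativity tasks before and after stimulation, with EEG and HRV recorded during the tasks. For the first battery it says: "In this part of the intervention, the creativity tasks will take place between the two physical tests". For the second: "physical, cognitive, and creativity tasks (in this order) will be performed again while EEG and HRV are recorded".

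Section 2.2.3 (Randomization) lists three randomised items: the order of the three intensities, the order of sub-tasks within balance and within strength, and whether the subtractions start from an even or an odd number. The place of the creativity block is not listed.

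Section 2.6 (Data Analysis) will test "differences between conditions (1 mA, 2 mA and sham), in all the outcomes" by Kruskal–Wallis, with Mann–Whitney tests post hoc. It does not say whether the analysed value is the post-tDCS value, a change or an adjusted value. It names no pre–post test.

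**The concern.** The two batteries do not measure the same thing under the same circumstances. Before tDCS, the creativity recordings follow one physical test; afterwards they follow both. Before tDCS, two 3-minute imagery tasks separate balance from strength; afterwards they do not. The strength test is real exertion: squats, familiarisation repetitions and six maximal-type repetitions (section 2.5.2). EEG and HRV are primary outcomes.

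The hypotheses are worded as improvement, and the Discussion expects less interference once stimulation has been given. That wording invites a reading of pre–post change within a condition, where order and fatigue cannot be separated from stimulation.

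The pre values are also the only measure of how a woman was performing on that day. If day-to-day variation matters in fibromyalgia, leaving it in the error costs precision in a trial with 13 women per group. A baseline taken under a different block order may track the post value less well.

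**Working it through.** **1. The plan's own figure.** Section 2.2.2 states that "a sample size of 13 achieves 99% power to detect a mean of paired differences of 3.5". Its other inputs are an SD of 2.5 for those differences, two-sided alpha 0.05, and a Wilcoxon test applied to normal data. The standardised difference is 3.5/2.5 = 1.4. The effective n for the Wilcoxon test is 13 × 3/π = 12.41, the noncentrality is 1.4 × √12.41 = 4.93, and the power is 99.4%. Simulating the exact signed-rank test (10,000 runs) gives 99.5%. The stated 99% reproduces, and nothing below changes it.

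**2. What a common order shift does.** Write pre = participant + session + error, and post = participant + session + new error + order shift o + stimulation effect δ. Then:
- change within sham has mean o;
- active minus sham change has mean (δ + o) − o = δ.

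Simulation with n = 13, 2,000 runs, no stimulation effect and total SD 1. The correlations are assumed: 0.6 between sessions and 0.8 pre–post within a session.

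| Order shift | Sham-only pre–post Wilcoxon rejects | Mean active − sham change |
|---|---|---|
| 0 | 4.5% | −0.003 |
| 0.3 SD | 35.0% | −0.011 |
| 0.5 SD | 73.1% | −0.003 |

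At a shift of 0.5 SD, rejection between conditions stays at about 5% or below for Kruskal–Wallis and Friedman tests, on post values or on change. The shift therefore distorts within-condition change and leaves the comparison between conditions intact.

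**3. What adjustment could gain.** The article gives no variance components, so the splits below are assumptions. Let s be the session share and r the residual share of total variance. For the paired difference between two conditions, in units of σ²/n:
- post only: 2(s + r);
- adjusted for the paired pre difference: 2(s + r) × [1 − (s/(s + r))²];
- with the slope estimated from 13 pairs, multiply by 1 + 1/(n − 3) = 1.10;
- raw change score: 4r.

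| Participant/session/residual (%) | Post only | Reduction, large sample | Reduction, n = 13 | Change score | Change vs post only |
|---|---|---|---|---|---|
| 60/20/20 (central) | 0.80 | 25% | 1 − 0.75 × 1.10 = 17.5% | 0.80 | none |
| 50/30/20 | 1.00 | 36% | 1 − 0.64 × 1.10 = 29.6% | 0.80 | 20% lower |
| 70/10/20 | 0.60 | 11% | 1 − 0.889 × 1.10 = 2.2% | 0.80 | 33% higher |
| 50/20/30 | 1.00 | 16% | 1 − 0.84 × 1.10 = 7.6% | 1.20 | 20% higher |

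Simulation of the adjusted contrast at n = 13 gave about 18%, 30%, 3% and 8%, in agreement. The central case is worth 1/0.825 = 1.21, or about a fifth more women. If s = 0 there is nothing to gain, and the slope costs about 10%. At n = 13 the break-even is s/(s + r) = √(1 − 1/1.10) ≈ 0.30.

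**4. When a change score helps.** With between-session correlation rb and within-session pre–post correlation rw, 4(1 − rw) < 2(1 − rb) requires rw > (1 + rb)/2. In the central split rw = 0.8 and (1 + 0.6)/2 = 0.8, so there is no gain.

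**The case against.** This is a condensed article and no statistical analysis plan is shown. A reader might infer that the pre values are discarded. The text does not say so; it is silent on the analysed value, and an unseen plan may define it. What stands is narrower: the named tests take no covariate, so a change score is the only way the pre value could enter them, and none is mentioned. The block order is a different matter, because it is stated outright. The timeline figure is not available to check it against.

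A reader might also infer that the order difference biases the comparison with sham. The documents do not support that. One script is described for every session, so an additive order effect is common to the three conditions and cancels. Only an interaction between order and stimulation would survive, and nothing in the article points to one.

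Nor is a loss of precision certain. It depends on correlations the article does not give. With other assumed correlations (0.5–0.8 between sessions, up to 0.9 within), the large-sample reduction runs from 0% to 64%, so 11–36% is not a bound.

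Finally, the figures take a paired contrast as benchmark, whereas section 2.6 names tests for independent samples. That is correct. They show what adjustment adds once the analysis respects the crossover; the use of unpaired tests is a separate point. The randomisation of sub-tasks in section 2.2.3 is not at fault.

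**Conclusion.** The point holds in a limited form. The batteries differ in block order, the difference is neither randomised nor explained, and the pre values have no stated role. Within-condition pre–post change cannot be attributed to stimulation: an assumed order shift of 0.5 SD alone would make a sham-only test significant about 73% of the time. The between-condition comparison is not biased by an additive shift.

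The likely benefit of adjustment at n = 13 is modest, about 2–30% less variance and 17–18% in the central case. It rests wholly on the assumed splits, and it vanishes when there is no session variance. The size of any real order or fatigue effect cannot be derived from the article, which gives neither posture during imagery nor the interval between batteries. The change is worth making because it is nearly free; the planned comparison does not fail without it.

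**What to change.** - Section 2.5.1: use the same block order before and after stimulation in all three sessions.
- Section 2.6: analyse the post-tDCS value with the same session's pre-tDCS value as covariate, in a within-participant model, so that the covariate acts on differences between a woman's own sessions.
- Section 2.6: state that pre–post change is interpreted only against sham.
- Do not make a raw change score the default. Use it only where rw > (1 + rb)/2 can be justified.

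The cost is one line in the session script and one covariate; no assessment is added. The downside is small: one slope to estimate with 13 women per group, and a model in place of a simple rank test.

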#### 2.5.2. Primary Outcomes

##### Neurophysiological Variables 

Electroencephalography (EEG) and Heart Rate Variability (HRV)

The Enobio^®^ instrument (Neuroelectrics, Cambridge, MA, USA) [61] and Neuroelectrics^®^ instrument driver software (NIC1) will be used to record EEG and HRV signals. The reliability of this device has been proven even when using “dry” electrodes [62]. Therefore, this device allows us to evaluate the EEG signal in 19 channels, according to the International System 10–20, in different brain areas: frontal (Fz, Fp1, Fp2, F3, F4, F7, and F8), central (Cz, C3, and C4), temporal (T3, T4, T5, and T6), parietal (Pz, P3, and P4), and occipital (O1 and O2). Two electrodes placed on the mastoids will act as a reference. The impedance will be kept below 10 KΩ during recording. In this regard, the sampling frequency is 500 Hz, with a 50 Hz notch filter and a bandpass filter from 1 to 40 Hz. In addition, to process data collected in DT, we will use the recommendations provided in the work of Cheron et al. [63] to perform EEG recordings in movement. In this respect, the ASR filter will be used [64]. 

Once the data has been collected, the Matlab toolbox, EEGlab, will be used to preprocess and analyze the data. Artifacts with a noncortical source (eye movements, muscle activity, or line noise) will be corrected by independent component analysis (ICA) [65]. Once all sources of artifacts have been corrected, using the pop_spectopo.m function of EEGlab, we will separate the signal into 6 different spectral power bands: theta (4–7 Hz), alpha-1 (8–10 Hz), alpha-2 (11–12 Hz), beta-1 (13–18 Hz), beta-2 (19–21 Hz), and beta-3 (22–30 Hz).

HRV data will be exported in .edf format to the Kubios HRV software (v. 2.1) [66]. Different HRV variables will be extracted: (a) time domain, such as mean HR (mean HR) RR, the standard deviation of the whole RR interval (SDNN), NN50 count divided by the total number of all NN intervals (Pnn50) and the square root of the mean of the sum of squares of differences between adjacent NN intervals (rMSSD); (b) frequency domain, which includes the ratio of low frequency (LF, 0.04–0.15 Hz)/high frequency (HF, 0.15–0.4 Hz) ratio (LF/HF) and total power; (c) nonlinear measures, such as entropy (ApEn and SampEn). 

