##### Physical Fitness

Balance

The tests will be performed on a Kistler force platform (Type 9286a, Kistler Instrumente AG, Winterthur, Switzerland), and the signal recording will be set at 200 Hz [67]. The sway area in cm², the mean amplitude from RMS (root mean square), and the mean velocity in the anteroposterior and mediolateral directions in cm/s will be recorded. In addition, the entropy (SampEn) in the anteroposterior and mediolateral directions will be obtained to determine the regularity with which the COP trajectory repeats [20,67].

Different static posturography tests will be performed to analyze the center of pressure (COP) pattern as well as to establish a sensory analysis of the visual, proprioceptive, and vestibular systems. The tests will be performed in a static position with eyes open (EO) and static position with eyes closed (EC). Each test will have a duration of 45 s [68], where the first 5 s will be considered as adjustment time before starting the recording [69].

Strength 

This test will be performed on the isokinetic dynamometer (Multi-Joint 3, Biodex Medical Systems, Inc., Shirley, NY, USA).

Isokinetic dynamometry (ID) allows for the measurement of the strength of the agonist and antagonist muscles at a given angular velocity [70]. From the execution of the test, the peak torque and average peak torque, average power, and total work power will be obtained [70,71,72]. The execution of the test consists of performing a concentric contraction of knee flexion and extension six times [70,72] consecutively and without pause between repetitions at a speed of 60/s and in a range of movement from 0 to 90 degrees, 0 degrees being full extension and 90 degrees being flexion [72]. 

Before the test, 10 squats will be performed as a warm-up. In addition, a familiarization phase with the test will be carried out, in which 10 consecutive repetitions of knee flexion and extension will be performed at a speed of 120/s. Before starting the final test, 1 min of rest time shall be given [73].

Dual-Task Condition

In DT conditions, participants will simultaneously perform the corresponding physical task (strength or balance) and a cognitive task. In this regard, the cognitive task will consist of two-by-two subtractions from a number greater than 100 [74].

Creativity

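### LF/HF, total power and entropy cannot be usefully estimated from the 18 to 45 s balance and strength tests, which supply every dual-task HRV value

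*Protocol article*

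**What the plan says.** In the protocol article, section 2.5.2 (Primary Outcomes, Neurophysiological Variables) carries the entry "Electroencephalography (EEG) and Heart Rate Variability (HRV". Its frequency-domain indices are "frequency domain, which includes the ratio of low frequency (LF, 0.04–0.15 Hz)/high frequency (HF, 0.15–0.4 Hz) ratio (LF/HF) and total power", followed by "nonlinear measures, such as entropy (ApEn and SampEn". The time-domain list contains mean HR, RR, SDNN, pNN50 and rMSSD. No index is assigned to a particular recording window.

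Section 2.5.1 says when the cardiac signal is taken. Before stimulation: "During the performance of these tests, brain and cardiac electrical activity will be recorded with EEG, and HRV". After stimulation: "physical, cognitive, and creativity tasks (in this order) will be performed again while EEG and HRV are recorded". For the two 5 min recordings before and after tDCS, the same section names EEG only. Section 2.4 also mentions recording HRV with EEG, in the paragraph on the 20 min stimulation.

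The test lengths are in 2.5.2. Balance: "Each test will have a duration of 45 s [68], where the first 5 s will be considered as adjustment time before starting the recording". Strength: six knee flexion-extension repetitions, "consecutively and without pause between repetitions at a speed of 60/s and in a range of movement from 0 to 90 degrees". The two imagery (creativity) tasks take 3 min each. Dual-task conditions are balance or strength performed with a subtraction task.

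**The concern.** A spectral band can be estimated only from a record that spans several cycles of its slowest component. The LF band starts at 0.04 Hz, or one cycle every 25 s. The strength test is shorter than one such cycle and a balance test is shorter than two. Entropy indices describe how patterns recur in a beat series, and here the series would be a few dozen beats.

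The trial centres on dual-task performance, and every dual-task HRV value comes from one of these tests. If the listed indices are extracted there, part of a primary outcome is close to noise in a sample of 13 women per group. Section 2.6 tests all outcomes under a Benjamini–Hochberg adjustment, so these values would also join the family that is adjusted.

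**Working it through.** The article gives no figure for the precision of HRV. Its only design figure, 99% power in 2.2.2 (n = 13, mean paired difference 3.5, SD 2.5), reproduces at 99.4% using the Wilcoxon efficiency factor 3/π. It plays no part in this point.

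**Inputs from the article.** LF band 0.04–0.15 Hz and HF band 0.15–0.4 Hz; balance 45 s with the first 5 s as adjustment; strength six repetitions over 90 degrees each way at 60/s (read as degrees per second); imagery 180 s; pre- and post-tDCS recordings 300 s; stimulation 1,200 s.

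**Assumptions.** Heart rate 60 to 100/min; no turnaround time between directions in the strength test; dual-task versions last as long as single-task versions.

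**Formulas.**
- Period at the lower edge: 1/0.04 = 25 s.
- Strength duration: 6 × 2 × 90/60 = 18 s.
- Balance, less adjustment: 45 − 5 = 40 s.
- Resolution = 1/T; cycles at the edge = 0.04 × T; LF bins = number of multiples k/T from 0.04 up to, but not including, 0.15 Hz; beats = T × rate/60.

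The last column is an illustrative simulation: 1,500 runs per window, Hann periodogram after detrending, a fixed assumed stationary spectrum and a true LF/HF of 1.0.

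| Window | T (s) | 1/T (Hz) | Cycles at 0.04 Hz | LF bins | Beats | Estimated LF/HF, 5th–95th percentile |
|---|---|---|---|---|---|---|
| Strength | 18 | 0.056 | 0.72 | 2 | 18–30 | 0.10–4.69 |
| Balance, less 5 s | 40 | 0.025 | 1.6 | 4 | 40–67 | 0.16–3.75 |
| Balance, full | 45 | 0.022 | 1.8 | 5 | 45–75 | 0.19–3.71 |
| Imagery task | 180 | 0.0056 | 7.2 | 19 | 180–300 | 0.45–2.09 |
| 5 min recording | 300 | 0.0033 | 12 | 33 | 300–500 | 0.54–1.74 |
| Stimulation | 1,200 | 0.0008 | 48 | 132 | 1,200–2,000 | 0.75–1.34 |

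At 18 s the resolution (0.056 Hz) is coarser than the band edge itself. The 95th percentile of the estimated ratio is about 47 times the 5th at 18 s and 23 times at 40 s, against about 3 times at 300 s. The simulation holds the spectrum constant, whereas knee effort would shift heart rate within the window.

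The result does not hinge on the turnaround assumption. If turnaround doubled the strength test to 36 s, it would still hold only 36 × 0.04 = 1.44 cycles. Running tests back to back does not give one longer segment, because the task conditions differ and their order is randomized.

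**The case against.** **Not all cardiac data are short.** This stands. HRV is also recorded in two 3 min imagery tasks before and after tDCS, and apparently during the 20 min stimulation; the length of the separate cognitive task is not given. A reader might infer that the whole autonomic outcome is confined to 18 to 45 s windows, and the article does not support that. The longer windows do not settle the matter, though. Recording during stimulation has no pre-tDCS counterpart. The imagery tasks sit between the two physical tests before tDCS but after the physical and cognitive tasks afterwards, so the preceding load differs. Neither supplies a dual-task value.

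**The results are not artefact.** A reader might infer that all autonomic results would be artefact, or that a false active-versus-sham difference would arise. The documents do not support this either. Mean HR remains usable and rMSSD is less affected. Every participant does the same tests under all three conditions, so window length and effort are common to active and sham. The harm is mainly lost precision and interpretability.

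**The window for each index may be set elsewhere.** An article can leave that to a fuller document, and naming only EEG for the 5 min recordings does not exclude a cardiac channel. This is fair as far as it goes. But the article does fix the indices, bands, tasks and durations, and that combination fails for balance and strength. A later analysis plan can drop indices; it cannot recover resting cardiac data that were not recorded.

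**Entropy.** The documents give no minimum number of beats, so that part is a judgement on a small count and not a derived limit.

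**Conclusion.** The point holds for the balance and strength tests, single- and dual-task. LF/HF and total power with a 0.04 Hz lower edge cannot be meaningfully estimated from 0.72 cycles (strength, 2 LF bins) or 1.6 to 1.8 cycles (balance, 4 bins at 40 s). ApEn and SampEn would rest on about 18 to 67 beats, taking 18 s and 40 s. That covers all dual-task HRV.

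It does not extend to the imagery tasks, to any recording during stimulation, or to mean HR. The durations and cycle counts follow from the article's own settings. The beat counts depend on the assumed heart rate, and the simulated ranges depend on the assumed spectrum and serve only to show the order of the loss. The change should be made before recording starts.

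**What to change.** State in 2.5.1 and 2.5.2 that the cardiac channel is recorded in both 5 min recordings, before and after tDCS, and name the window that supplies each index:

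- LF/HF, total power, SDNN, ApEn and SampEn from the two 5 min recordings. These match in length, and each comes before the physical tests of its own block.
- The same indices from the 3 min imagery tasks as supportive only, because the position of those tasks relative to the physical tests differs before and after tDCS.
- In the balance and strength tests, mean HR/RR, with rMSSD at most.

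**Cost.** No visit time is added, since the same instrument records both signals. The real loss is that LF/HF and entropy are no longer reported under dual task. The introduction names neurophysiological variables during dual-task performance as a gap in knowledge, so the article should say openly that dual-task HRV is limited to heart rate and, at most, rMSSD.
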